**3.4. Sampling**

Musina municipality will be purposefully selected from Vhembe District. These are in geographic proximity of the University of Venda where researcher is located and where the previous study was conducted ([name] *et al*., 2015). Simple random sampling will be used to select six preschools, three each from the two local municipalities. Simple random sampling is a sampling procedure, which provides equal opportunity of selection for each element in a population (Lee and Nieman, 2010). A list of pre-schools will be obtained from the Department of Social Development in Vhembe district and each pre-school will be assigned a number. The researcher will randomly select one number at a time. The following Slovin formula is used to calculate the total sample size used in the study: n = N/ (1 + (N X e^2^)) where

n= sample size

N= total number of children in the pre-schools; and

e = the accepted level of error

n = N/ (1 + (N X e^2^))

=40291/ (1+(40291 x 0.05)

=40291/ 101.7275.

= 396

= plus 10%

= 435.6

= 436

The formula yielded 396 participants, and an additional 10% will be added to account for attrition, making 436. Total sample size was calculated from the total number of children registered in the Early Childhood Development under Social Development in South Africa in 2017 in Vhembe district (Government Gazette, 2017). The sample frame will be six preschools, which are yet to be randomly selected. If the total number of participants in these six selected preschools does not reach the total number of 436, two more preschools will be added to the sample frame. The six preschools will be randomly assigned to the treatment or control.

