**3.6.3.2. Objectives**:

3.6.3.2.1. To feed the children with the intervention or control for six months

- - - - 1. To assess adherence to the dietary intervention in terms of consuming Cucurbita *moschata* seed paste

**3.6.3.3. Design:** Study design will be a pretest-posttest control group trial, using cluster randomisation, which is a type of scientific experiment, which aims to reduce bias when testing a new treatment (Leedy and Ormrod, 2010). The preschools participating in the trial are randomly allocated either to the group receiving the treatment under investigation or to a group receiving standard treatment (or placebo treatment) as the control (Leedy and Ormrod, 2010). Randomized minimizes selection bias and the different comparison groups allow the researchers to determine any effects of the treatment when compared with the no treatment (control) group, while other variables are kept constant (Leedy and Ormrod, 2010). Randomization will take place at the preschool level. The research will be using single blinded trial with a knowledge of who is receiving the treatment amongst the participants.

- - - 1. **Intervention and data collection:**

The experimental group will receive their normal diet plus paste (grounded *Cucurbita moschata* seeds mixed with cooked *Cucurbita moschata* flesh) and the educational lesson through the song for six (6) months while the control group will receive normal diet plus mashed *Cucurbita moschata* flesh. The participants will consume ½ cup (64 g) (***to be confirmed after development and pilot***) paste (grinded *Cucurbita moschata* seeds mixed with mash *Cucurbita moschata* flesh) twice per week, during lunch with their normal diet while the control will consume mashed *Cucurbita moschata* flesh at the preschool sites over a six (6) month period. Two dishes made from grinded *Cucurbita moschata* seeds mixed with *Cucurbita moschata flesh* will be used to bring variety and improve compliance.

Grounded *Cucurbita moschata seeds* will be packaged at the food science laboratory at the university of Venda before being delivered to preschools. The packaged grounded *Cucurbita moschata seeds will be mixed with cooked Cucurbita moschata flesh at the preschool site. Mashed Cucurbita moschata flesh mixed with grinded seeds and Mashed Cucurbita moschata flesh* will be served to children during their lunchtime under the supervision of the researcher and trained field worker.

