**Table 3.3: Schematic representation of the feeding trial.**

| **Group** |  | **Estimated no** | **Intervention** | **Intervention days (three teams)** | **Quality control** |
| --- | --- | --- | --- | --- | --- |
| Experimental | Preschool 1 | 73 | Normal diet plus seed paste.  Song | Monday  Wednesday | Plate wastage observations and adherence recording |
|  | Preschool 2 | 73 | Normal diet plus seed paste  Song | Tuesday  Thursday | Plate wastage observations and adherence recording |
|  | Preschool 3 | 73 | Normal diet plus seed paste  Song | Monday  Thursday | Plate wastage observations and adherence recording |
|  | Preschool 4 | 73 | Normal diet plus seed paste  Song | Wednesday  Friday | Plate wastage observations and adherence recording |
| Control | Preschool 5 | 73 | Normal diet plus mashed butternut (placebo) | Monday  Wednesday | Plate wastage observations and adherence recording |
|  | Preschool 6 | 73 | Normal diet plus mashed butternut (placebo) | Tuesday  Thursday | Plate wastage observations and adherence recording |
|  | Preschool 7 | 73 | Normal diet plus mashed butternut (placebo) | Monday  Thursday | Plate wastage observations and adherence recording |
|  | Preschool 8 | 73 | Normal diet plus mashed butternut (placebo) | Wednesday  Friday | Plate wastage observations and adherence recording |

The intervention will be implemented over six months or 180 days. On intervention days, Monday to Thursday, the field workers and the researcher will be on site for quality control. They will work in teams of two, one team per preschool. The researcher will change team daily to ensure standardisation and quality control**.**

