**3.6.3.5. Monitoring and quality control**

Plate wastage and consumption adherence will be monitored and recorded by trained field workers. Monitoring for plate wastage and adherence will be done each day randomly. In order to assess the plate wastage and adherence on the consumption of *Cucurbita moschata* seeds **Appendix E** will be used for recording. Trained field workers will record amount given and remaining after feeding on randomly selected children, ten each time, they will be expected to do this twice a week. To assess the consumption of other iron and zinc rich foods, the parents/caregivers will be requested to fill out a food dairy to record for food consumed by their children at home. A food diary will be given to parents/caregivers to record food that is been given to children at home. This will help to monitor the compliance on the consumption of iron and zinc rich food. They will be asked to fill one day per week covering all seven-week days over 6 months (**see Appendix F)**. Sensory evaluation will be done once a month in the experimental preschools by the researcher at the preschool site.

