**3.7. Fieldworkers**

Five nutritionists will be recruited for monitoring, implementation of the feeding trial. The researcher will train field workers and methods of data collection will be standardized during piloting. The total team will be six including the researcher. Phlebotomist will be responsible for drawing blood as it is a requirement by the Health Professional Council of South Africa and these will be provided as part of the package from Ampath laboratories. The appointment of fieldworkers will be based on their expertise, which will be required for the study and for good general practice. There will be three teams with each visiting one primary school on the day of the feeding trial for monitoring. The table below illustrates the data collection responsibilities.

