**Table 3.6: Personnel responsibilities during data collection**

| **PERSON RESPONSIBLE** | **Phase 1: Development of an intervention** | **Phase 2: Implementation of NE, NSFP meal and dish** | | |
| --- | --- | --- | --- | --- |
|  |  | **Phase Two** | **Phase 3:**  **Implement intervention** | **Phase 4:**  **Evaluate efficacy** |
| Promoters | Quality control | Quality control | Quality control | Quality control |
| Researcher | Recipe development and standardization  Training of field workers  Feedback meetings with promoters and quality control  Transport dishes for nutrient and microbial analysis | Arrange all resources needed for data collection car, equipment, pens etc.  Data collection with field workers  Feedback meetings with promoters and quality control  Data capturing and analysis | Purchasing of ingredients for preparation of Snack  Provide snack for preschools  Provide nutrition education using song  Quality control once every two weeks | Arrange all resources needed for data collection car, equipment, pens etc.  Data collection with field workers  Feedback meetings with promoters and quality control  Data capturing and analysis |
| Field workers  Nutritionist | Form part of the team  Assist in sensory evaluation  Pilot | Anthropometric measurements Questionnaire  Data capturing and cleaning | Intervention implementation Prepare the dishes  Serve the children  Data collection  Compliance  Plate waste studies | Questionnaires  Anthropometric measurements  Data capturing and cleaning |
| Field worker-  Phlebotomist | N/A | Draw blood  Transport to the lab storage and analysis | N/A | Draw blood and transport to the lab for storage and analysis |
| Pre-School teacher/principal | N/A | Subject recruitment  Allocate space | Receive ingredients/food  Monitoring | Participate in monitoring and quality control |

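### The printed feeding timetable cannot be staffed: three teams working Monday to Thursday cover 11 of 16 weekly feeds at eight preschools, and 8 to 11 of 12 at six

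*Protocol*

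**What the plan says.** Section 3.4 plans six preschools. Only if these do not yield 436 children, "two more preschools will be added to the sample frame". The schematic in section 3.6.3 nevertheless prints eight, at 73 children each, with these feeding days:

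- Preschools 1 and 5: Monday and Wednesday
- Preschools 2 and 6: Tuesday and Thursday
- Preschools 3 and 7: Monday and Thursday
- Preschools 4 and 8: Wednesday and Friday

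The heading of the days column refers to three teams. The text below the table reads "On intervention days, Monday to Thursday, the field workers and the researcher will be on site for quality control", and then "They will work in teams of two, one team per preschool". Section 3.7 agrees on capacity: "The total team will be six including the researcher", and "There will be three teams with each visiting one primary school on the day of the feeding trial for monitoring". The budget in section 3.10 pays five nutritionists for four days a week.

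The teams deliver the intervention as well as observe it. Under section 3.6.3 the food "will be served to children during their lunchtime under the supervision of the researcher and trained field worker". The phase-three entry for field workers in Table 3.6 begins "Intervention implementation Prepare the dishes" and goes on to serving, compliance and plate-waste work.

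**The concern.** The timetable, the number of teams and the working days are all fixed in the protocol, and they do not fit together. Two preschools have a Friday feed when no team is on site. Three other weekdays need four teams where three exist. Because feeding takes place at lunch and each team is assigned to one school, a team cannot be assumed to cover a second site on the same day.

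At stake are delivery of the intervention and the adherence record. Assessing adherence is a stated objective of phase three. With two feeds a week, one missed feed would halve a child's exposure for that week. The protocol does not say which site goes without a team on an over-booked day, or what happens to its feed, so field staff would have to decide.

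**Working it through.** **Capacity.** Section 3.7: (5 nutritionists + 1 researcher) / 2 = 3 teams, which reproduces the stated number. Weekly capacity is 3 teams × 4 days = 12 visits. The budget agrees: 5 people × R150 × 16 days × 9 months = R108 000, the printed amount, with 16 days a month being four days a week. No Friday work is funded.

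**Eight preschools as printed.** Visits staffed on a day = the smaller of 3 and the visits needed, Monday to Thursday; Friday = 0.

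| Day | Preschools | Needed | Staffed |
|---|---|---|---|
| Monday | 1, 3, 5, 7 | 4 | 3 |
| Tuesday | 2, 6 | 2 | 2 |
| Wednesday | 1, 4, 5, 8 | 4 | 3 |
| Thursday | 2, 3, 6, 7 | 4 | 3 |
| Friday | 4, 8 | 2 | 0 |
| Total | | 16 | 11 |

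Five of 16 feeds (31%) have no team. Working Fridays would raise the count to 13 of 16. On any timetable, eight preschools need 16 visits against 12 on four days or 3 × 5 = 15 on five.

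**Six preschools.** Section 3.4 plans six, and the printed 73 per school matches six: 436 / 6 = 72.7, and 6 × 73 = 438, whereas 8 × 73 = 584. The protocol does not say which two rows are the reserve, so all 28 choices of six rows were counted:

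- Rows 4 and 8 dropped: Monday 4, Tuesday 2, Wednesday 2, Thursday 4; staffed 3 + 2 + 2 + 3 = 10 of 12.
- Rows 1 to 6 kept: Monday 3, Tuesday 2, Wednesday 3, Thursday 3, Friday 1; staffed 3 + 2 + 3 + 3 + 0 = 11 of 12.
- Rows 2 and 6 dropped: Monday 4, Wednesday 4, Thursday 2, Friday 2; staffed 3 + 3 + 2 + 0 = 8 of 12.
- All 28 choices: 8 to 11 of 12, with 10 in 17 of them. With three rows kept per arm (16 choices), the range is the same and 10 occurs in 9.

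Twelve is never reached. Keeping row 4 or row 8 brings in an unstaffed Friday, and dropping both leaves four visits on Monday and on Thursday.

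**Split by arm.** In the eight-row table each four-visit day has two experimental and two control sites. Three teams must cover these 2:1.

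**Dose, as outer limits only.** If preschool staff serve every unstaffed feed, children still receive 2.00 feeds a week. If every unstaffed feed is missed, the mean is 11 × 2 / 16 = 1.38 with eight preschools, and 10 × 2 / 12 = 1.67 with six if rows 4 and 8 are the reserve.

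**The case against.** The strongest reply is that this is a rota slip in a table labelled schematic. The planned design needs 12 visits and three teams supply 12, so only the spread of days is wrong. Eight preschools arise only if recruitment falls short. Section 3.6.1.8 leaves portion size and feeding frequency to phase one, so the timetable must be revisited anyway. This stands, and it is why the point is minor. It does not remove the conflict between the printed days and the stated staffing.

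Three stronger readings are tempting, and the documents support none of them.

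- **Every unstaffed feed is lost.** Table 3.6 gives the preschool teacher or principal a role in receiving food and in monitoring during phase three, and ground seed is packaged before delivery. Some feeds could go ahead without a team. The supervision wording is also loose, since one researcher moving between three teams cannot attend every feed on any timetable.
- **A countable share of plate-waste records is lost.** Section 3.6.3.5 describes sampling: "ten each time, they will be expected to do this twice a week". If that quota applies to each team, three teams could meet it in full.
- **The arms are affected equally because their printed days match.** Matching days mean matching demand, not matching coverage. With a 2:1 split on four-site days, coverage could differ by arm unless the omitted site alternates, and the protocol has no such rule. Nor does it show that coverage would differ, so bias is possible but not established.

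**Conclusion.** The point holds as a minor inconsistency. The printed timetable cannot be carried out with the stated teams and days: 11 of 16 weekly feeds can be staffed at eight preschools, and 8 to 11 of 12 at six. The figure of 10 of 12 rests on the unstated assumption that preschools 4 and 8 are the reserve sites; the conclusion that full coverage is never reached does not. All counts assume one site per team per feeding day, as sections 3.6.3 and 3.7 say. Unstaffed feeds would lack the planned preparation, supervision and adherence recording. The size of any loss of dose, and whether it would differ between arms, cannot be determined from the protocol.

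**What to change.** For the planned six preschools, change two cells of the schematic before feeding starts: preschool 3 from Thursday to Wednesday, and preschool 7 from Monday to Tuesday. Preschools 1, 3 and 5 are then fed on Monday and Wednesday, and 2, 6 and 7 on Tuesday and Thursday. That is three visits a day, 3 × 4 = 12 of 12 staffed, and no Friday.

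Mark rows 4 and 8 as contingency. State in section 3.4 that eight preschools need 16 visits against a capacity of 12 (15 if Friday is worked), so the printed timetable must not be used if the two extra sites are added. That case needs a new timetable and more staff time. Recount the visits if phase one changes the feeding frequency; three feeds a week at six preschools would need 18.

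The change for six preschools adds no staff, days or budget. It has two small costs. Weekdays are no longer mirrored between arms: Monday/Wednesday has two experimental sites and one control, and Tuesday/Thursday one and two. All 12 visits are used, so there is no spare team to cover an absence.

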**3.6.3.5. Monitoring and quality control**

Plate wastage and consumption adherence will be monitored and recorded by trained field workers. Monitoring for plate wastage and adherence will be done each day randomly. In order to assess the plate wastage and adherence on the consumption of *Cucurbita moschata* seeds **Appendix E** will be used for recording. Trained field workers will record amount given and remaining after feeding on randomly selected children, ten each time, they will be expected to do this twice a week. To assess the consumption of other iron and zinc rich foods, the parents/caregivers will be requested to fill out a food dairy to record for food consumed by their children at home. A food diary will be given to parents/caregivers to record food that is been given to children at home. This will help to monitor the compliance on the consumption of iron and zinc rich food. They will be asked to fill one day per week covering all seven-week days over 6 months (**see Appendix F)**. Sensory evaluation will be done once a month in the experimental preschools by the researcher at the preschool site.

**3.6.3.6. Data analysis**

A record of consumption will be kept on whether the children did consume mashed *Cucurbita moschata* flesh mixed with grounded *Cucurbita moschata* seeds and will be recorded in frequencies taking into consideration the wastage. Plate wastage observations will be quantified from the adherence record and plate wastage studies. Thematic analysis will be used to synthesize and interpret the observed data. Frequencies will also be used for food patterns analyses from the food diary using SPSS version 24 or latest.

A short quiz with two questions on the importance of the *Cucurbita moschata* seeds will be created to test the effectiveness of the song. The researcher conducts the quiz at the end of the six months with the children and analyse the findings.

**3.6.4.** **PHASE FOUR: POST FEEDING TRIAL**

**3.6.4.1. Aim:** To determine efficacy of *Cucurbita moschata* seeds on iron and zinc status of preschool children.

**3.6.4.2.** **Objectives**

3.6.4.2.1. To determine the demographic and environmental factors of the participants.

3.6.4.2.2. To measure the anthropometry of the study participants (Weight, Height, MUAC)

3.6.4.2.3. Determine the dietary diversity score of participants using 24- hour recall.

3.6.4.2.4. Determine dietary patterns of the study participants using FFQ.

3.6.4.2.5. To determine serum zinc concentrations among pre-school children using flame atomic absorption spectrophotometer before consuming *Cucurbita moschata* seeds.

3.6.4.2.6. To determine the iron status of pre-school children using hemoglobin, serum ferritin, transferrin receptor and C- reactive protein (CRP) before consuming the *Cucurbita moschata* (butternut) seeds.

**3.6.4.3. Design:** The study design will be post trial cross-sectional survey, similar to phase two. Quantitative data will be collected.

**3.6.4.4. Measurements, procedures and analysis**

The following measurements will be done: demographic and environmental factors, anthropometrics, dietary intakes and patterns, and biochemical data. Same parameters and procedures, which were done at the baseline and described in section 3.6.2.4, will be followed. Data will be analysed using same procedures as described for baseline, with addition regression and ANOVA to measure changes from baseline to post intervention, and between experimental and control. See table 3.5 below. This is done to determine the changes in nutritional status that is likely to have occurred because of the intervention. A statistician will be consulted.

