**Table 3.5: Proposed data analysis table**

| **Descriptive Statistics** | **Categorical data** | **Numerical data** | |
| --- | --- | --- | --- |
|  |  | **Normally distributed** | **Non-normally distributed** |
| ***Socio demographic information***   - Age - Gender   ***Anthropometric measures***   - Weight, height, MUAC - Categorization according to Z-scores: height for age, weight for age and BMI for age   ***Nutrient intake from 24hr recall***   - Total intake, - Consumption pattern   ***Dietary patterns***  Frequency of inclusion of food item in the FFQ  Morbidity diary  **Biochemical measures**   - Serum zinc - haemoglobin - Serum Ferritin - C-reactive protein - Transferrin saturation - Serum ferritin | Frequencies n (%) | Mean $\pm$ SD | Median and IQR |
| ***Analytical statistics-*** |  |  |  |
| ***Comparison of micronutrient status by subject characteristics*** | Pearson’s Chi-square test/Fishers exact test | ANOVA/T-test | Kruskal-Wallis/Mann-Whitney U tests |
| ***Association between dietary intakes and micronutrient status*** | Regression analyses with dietary intakes and anthropometric indices as dependent variables and all other as independent | | |
| ***Validation of dietary intake and micronutrient status against the intervention*** | Spearman’s correlation coefficient  Comparison of means/means Weighted kappa statistic for agreement testing  Bland Altman plots for bias and agreement testing | | |

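### Preschools are randomised, but the regression and ANOVA named for the arm comparison have no preschool term, so a child-level test is anti-conservative if outcomes are correlated within preschools.

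*Protocol*

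**What the plan says.** Section 3.6.3.3 of the protocol describes a "pretest-posttest control group trial, using cluster randomisation" and adds: "Randomization will take place at the preschool level". Section 3.4 says: "The six preschools will be randomly assigned to the treatment or control". It does not say how many go to each arm. It also provides that, if enrolment falls short, "two more preschools will be added to the sample frame". The schematic of the feeding trial in section 3.6.3 already lists eight preschools, four per arm, down to "Preschool 8 | 73" children.

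For the final comparison, section 3.6.4.4 applies the baseline procedures "with addition regression and ANOVA to measure changes from baseline to post intervention, and between experimental and control" and refers to Table 3.5. That table lists "Pearson’s Chi-square test/Fishers exact test" for categorical data, ANOVA or a t-test for normal data, and "Kruskal-Wallis/Mann-Whitney U tests" for non-normal data. The row is labelled as a comparison of micronutrient status across subject characteristics, not across arms.

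No section mentions a preschool effect, mixed model, GEE, cluster-level summary, ICC or design effect. Section 3.6.4.4 says a statistician will be consulted; the plan of action in section 3.12 places this in January 2022, after post-intervention data collection in November 2021.

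**The concern.** When preschools are allocated, the evidence on the arm effect comes from a handful of preschools. Children in one preschool share a menu and staff, and their study food is mixed on site, so their outcomes are likely to be correlated. A standard regression or ANOVA on children counts each child as a separate piece of evidence and puts ordinary variation between preschools into the apparent effect of the seeds.

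This bears on the primary aim, efficacy on zinc and iron status. A chance difference between a few preschools could be reported as an effect of the intervention. It is also more than a detail left to an analysis plan: the protocol names the methods for the arm comparison, and as named they do not match its own randomisation.

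**Working it through.** **Inputs from the protocol.** N = 40291 children and e = 0.05 (section 3.4); total 436; six preschools (section 3.4) or eight of 73 (feeding-trial table).

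**Assumed, because the protocol does not give them.** ICC 0.01 to 0.10; a two-sided nominal 5% level; an equal split, 3 v 3, for six preschools (4 v 4 is shown for eight).

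**The plan's own figure.** n = N/(1 + N·e²) = 40291/101.7275 = 396.07, so 396; 396 × 1.10 = 435.6, so 436. This reproduces. The printed line omits the square on 0.05, but the denominator uses it. The formula has no term for clustering. Per preschool, 436/6 = 72.7. The feeding-trial table implies 8 × 73 = 584.

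**Formulas.** Design effect DE = 1 + (m − 1)·ICC. Effective N = total/DE. Actual error of a nominal 5% child-level test = 2·[1 − Φ(1.96/√DE)]. Interval ratio (preschool-level over child-level) = √DE × t(0.975, df)/1.96, with df = preschools − 2.

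Example, six preschools at ICC 0.01: DE = 1 + 71.7 × 0.01 = 1.72; √DE = 1.31; 1.96/1.31 = 1.50; error = 13.5%. With t(4 df) = 2.776, the interval ratio is 1.31 × 2.776/1.96 = 1.86.

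| Preschools × children | ICC | DE | Effective N | Actual error | Interval ratio |
|---|---|---|---|---|---|
| 6 × 72.7 (436) | 0.01 | 1.72 | 254 | 13.5% | 1.86 |
| 6 × 72.7 | 0.05 | 4.58 | 95 | 36.0% | 3.03 |
| 6 × 72.7 | 0.10 | 8.17 | 53 | 49.3% | 4.05 |
| 8 × 73 (584) | 0.01 | 1.72 | 340 | 13.5% | 1.64 |
| 8 × 73 | 0.05 | 4.60 | 127 | 36.1% | 2.68 |
| 8 × 73 | 0.10 | 8.20 | 71 | 49.4% | 3.57 |

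Even an ICC of 0.005 gives 9.3% in both layouts.

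**Sensitivity to preschool size.** With 396/6 = 66 children per preschool, the errors at ICC 0.01, 0.05 and 0.10 are 12.7%, 34.2% and 47.4%. With 436 spread over eight (54.5 each) they are 11.4%, 30.7% and 43.7%.

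**Simulation** (4,000 runs per setting, six preschools of 73). The child-level t-test rejects in 4.8% of runs at ICC 0, 14.2% at 0.01, 35.8% at 0.05 and 50.1% at 0.10. The inflation therefore comes from clustering alone. A t-test on preschool means rejects in 4.5% to 5.5% of runs across all settings with six or eight preschools.

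**Detectable difference** (80% power, six preschools, 436 children, preschool-level t-test): 0.47 SD at ICC 0.01, 0.77 at 0.05 and 1.03 at 0.10, against 0.27 SD if children were independent.

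**The case against.** The strongest reply is that the protocol says only regression, does not exclude a preschool term, and promises to consult a statistician; an analysis plan may add the term. That softens the charge but does not remove it. No such term is stated, and the consultation is timed after data collection, when the number of preschools can no longer be changed.

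Second, section 3.6.4.4 looks at changes from baseline, in which stable differences between preschools cancel. This stands as a limit on size: the relevant ICC is that of the change, which may differ from that of the level. The formulas apply to either, and small values already matter.

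Third, the size rests on assumptions. The ICC and the 3 v 3 split are not in the protocol, and 73 per preschool includes the attrition allowance. The smaller preschool sizes checked lower the figures somewhat and leave the conclusion unchanged.

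Several stronger readings are tempting and are not supported:

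- A reader might infer that a stated 5% error rate and planned confidence intervals are wrong. The protocol states no significance level (its 0.05 is the margin in the survey formula) and plans no intervals.
- A reader might take every test in Table 3.5 as a between-arm test. The row is labelled by subject characteristics and reaches the arm comparison only through the cross-reference in section 3.6.4.4.
- A reader might cite season or a shared time of blood draw as causes of correlation. One calendar covers all preschools, feeding days are mirrored across the arms, and Appendix B records the time of the blood draw for each child.

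**Conclusion.** The point holds in this limited form. The randomisation is by preschool, the methods expressly tied to the arm comparison carry no preschool term, and following the plan as written gives an anti-conservative test whenever the ICC is above zero. The true inflation is unknown because the protocol offers no ICC; under the assumed range of 0.01 to 0.10 it is large, from about 13.5% to 49% against a nominal 5%. Having eight rather than six preschools of about 73 does not reduce it. Because it affects the primary aim and is simple to correct on paper, it should be corrected before any comparison of arms is made.

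**What to change.** In section 3.6.4.4, and in Table 3.5 wherever its tests are used to compare arms, name a single primary between-arm analysis that respects the preschool. A suitable choice is a t-test on baseline-adjusted preschool means, with 4 df for six preschools or 6 df for eight, and preschool-level proportions for binary outcomes. Give a mixed model (arm fixed, preschool random intercept, baseline value as covariate, Kenward-Roger or Satterthwaite df) as supporting analysis. Fixing which is primary matters because the two can differ with so few preschools. Uncorrected sandwich or GEE standard errors should not be used with six to eight clusters.

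Reconcile six against eight preschools and 436 against 584 children, and state the allocation per arm. The count has consequences: an exact two-sided permutation test cannot go below 2/C(6,3) = 2/20 = 0.10 with 3 v 3, or 2/C(8,4) = 2/70 = 0.029 with 4 v 4.

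The text change is small, but the cost in precision is real. With six preschools, intervals are about 1.9 to 4 times as wide at ICC 0.01 to 0.10; with eight of 73, about 1.6 to 3.6 times. The detectable difference should be restated on this basis, and it may show that six preschools are too few.
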